## Abstract

**Background:**

Most subsequent new primary or recurrent melanomas might be self-detected if patients are trained to systematically self-examine their skin and have access to timely medical review (patient-led surveillance). Routinely scheduled clinic visits (clinician-led surveillance) is resource-intensive and has not been shown to improve health outcomes; fewer visits may be possible if patient-led surveillance is shown to be safe and effective. The MEL-SELF trial is a randomised controlled trial comparing patient-led surveillance with clinician-led surveillance in people who have been previously treated for localised melanoma.

**Methods:**

Stage 0/I/II melanoma patients (*n* = 600) from dermatology, surgical, or general practice clinics in NSW Australia, will be randomised (1:1) to the intervention (patient-led surveillance, *n* = 300) or control (usual care, *n* = 300). Patients in the intervention will undergo a second randomisation 1:1 to polarised (*n* = 150) or non-polarised (*n* = 150) dermatoscope. Patient-led surveillance comprises an educational booklet, skin self-examination (SSE) instructional videos; 3-monthly email/SMS reminders to perform SSE; patient-performed dermoscopy with teledermatologist feedback; clinical review of positive teledermoscopy through fast-tracked unscheduled clinic visits; and routinely scheduled clinic visits following each clinician’s usual practice. Clinician-led surveillance comprises an educational booklet and routinely scheduled clinic visits following each clinician’s usual practice.

The primary outcome, measured at 12 months, is the proportion of participants diagnosed with a subsequent new primary or recurrent melanoma at an unscheduled clinic visit. Secondary outcomes include time from randomisation to diagnosis (of a subsequent new primary or recurrent melanoma and of a new keratinocyte cancer), clinicopathological characteristics of subsequent new primary or recurrent melanomas (including AJCC stage), psychological outcomes, and healthcare use. A nested qualitative study will include interviews with patients and clinicians, and a costing study we will compare costs from a societal perspective. We will compare the technical performance of two different models of dermatoscope (polarised vs non-polarised).

**Discussion:**

The findings from this study may inform guidance on evidence-based follow-up care, that maximises early detection of subsequent new primary or recurrent melanoma and patient wellbeing, while minimising costs to patients, health systems, and society.

**Trial registration:**

Australian New Zealand Clinical Trials Registry (ANZCTR): ACTRN12621000176864. Registered on 18 February 2021.

**Supplementary Information:**

The online version contains supplementary material available at 10.1186/s13063-021-05231-7.

## Administrative information

The order of the items has been modified to group similar items (see http://www.equator-network.org/reporting-guidelines/spirit-2013-statement-defining-standard-protocol-items-for-clinical-trials/).

## Introduction

### Background and rationale {6a}

Melanoma incidence continues to increase in many countries worldwide. In Australia, the total number of people diagnosed with new melanomas increased from 3526 in 1982 to 14,485 in 2016, and the age-standardised rate increased from 27.9 per 100,000 in 1982 to 54 per 100,000 in 2016 [1]. This appears to be largely driven by increased early detection of early-stage melanoma before it has spread from the skin (in situ (stage 0) melanoma, and stage I–II invasive melanoma, together > 95% of all new melanoma diagnoses in Australia) [2]. After surgical excision of the melanoma, these patients are at risk of developing a subsequent new primary melanoma, a recurrence of their treated primary melanoma, and new keratinocyte (non-melanoma) skin cancers. Therefore, it is typically recommended that they undergo at least 10 years follow-up (and often longer), at intervals ranging from 3 to 12 months depending on melanoma stage [3, 4]. Patients diagnosed with an early-stage melanoma have a very good prognosis in terms of life expectancy: those with melanoma in situ (stage 0) have the same mortality risk as the general population, and those with thin melanomas (< 0.8 mm, which accounts for 65% of all invasive melanomas) have a 20-year survival of 80–96% [5–7]. Clinician-led surveillance in the form of routinely scheduled clinic visits is widely accepted as the usual model of follow up care after removal of a melanoma, under the assumption that this leads to earlier detection and treatment a subsequent new primary or recurrent melanoma, and reduced mortality. However, there is no direct evidence that clinician-led surveillance leads to improved survival [4, 8].

There is a need to balance the potential benefits of clinician surveillance for a subsequent new primary or recurrent melanoma, and keratinocyte skin cancers, against costs and possible psycho-social harms of frequent routinely scheduled clinic visits and investigations [9, 10]. The costs of follow-up for early-stage melanoma are substantial and have been estimated at AU$44 M over 5 years for American Joint Committee of Cancer (AJCC7) stage I/II [11]. Routinely scheduled clinic visits also cause opportunity costs in terms of clinician and patient time and could cause delays in the assessment of new patients who might benefit from more timely evaluation and treatment. Patients also incur travel and parking expenses, which may be especially burdensome for those who do not live close to the treatment centre. Fewer routinely scheduled clinic visits may have little impact on the detection of subsequent new primary or recurrent melanomas [12] and could result in substantial cost savings [13–15].

In addition to these considerations, the ongoing climate emergency and novel coronavirus (COVID-19) pandemic are both contributing to a growing and urgent need to re-consider how healthcare service is delivered [16, 17]. Other models of follow-up, including those using telehealth, present an opportunity to potentially decrease low value or unnecessary care [18], reduce environmental impacts of healthcare [17], and reduce nosocomial infection risk [19]. Telehealth may be especially valuable in the Australian context where a up to 30% of the population live remote to the major cities [20].

Patient-led surveillance is a new model of follow-up care for patients with a history of early-stage melanoma. Compared to the traditional clinician-led approach, there is increased reliance on patient self-management of their melanoma risk, with increased support for skin self-examination (SSE), fast-tracked access to unscheduled clinic visits should the patient identify a concerning lesion, and the potential for fewer routinely scheduled clinic visits [21]. Self or partner-detection of abnormalities may allow early detection of a subsequent new primary or recurrent melanoma, which may increase the effectiveness of treatment, and improve survival [22–25]. Although SSE is universally recommended by clinical guidelines, SSE education and practice remain suboptimal [21, 26]. Studies to date suggest that few people carry out SSE thoroughly and many fail to complete important components such as checking hard-to-see locations like the scalp, seeking assistance from someone else, and documenting changing lesions [27]. Previous survey and interview studies with people undergoing melanoma follow-up have shown a need for increased support for SSE, and acceptance of decreased frequency of routinely scheduled follow-up if recommended by their clinician [21, 28]. Additionally, clinicians are more likely to recommend fewer routinely scheduled clinic visits if they are confident of the patient’s ability to conduct SSE [29].

Digital technologies offer accessible platforms to facilitate SSE support and consolidate the behaviour changes needed for patient-led surveillance. Smartphone and web-based applications (apps) can prompt, remind, instruct, and record results from SSE, and facilitate teledermoscopy through the transmission of digital images taken by the patient, to a dermatologist for review. The Achieving Self-directed Integrated Cancer Aftercare (ASICA) Skin Checker app has been found to be feasible and acceptable for supporting SSE and triaging clinical review [30]. Studies on the preliminary assessment of diagnostic accuracy of patient-performed mobile teledermoscopy have demonstrated feasibility and acceptability for skin surveillance [31, 32]. Our pilot randomised controlled trial in patients with early-stage melanoma (*n* = 100) demonstrated the feasibility of a patient-led surveillance intervention that incorporated both the ASICA app and patient-performed mobile teledermoscopy (manuscript in preparation) [33]. This intervention also appeared to improve knowledge, attitudes, and practice of SSE, and to increase the early detection of subsequent new primary melanomas, with no adverse psychological outcomes. A larger sample is needed to confirm or refute these preliminary findings on the effects of patient-led surveillance.

To address these evidence gaps, we will conduct the MELanoma SELF surveillance (MEL-SELF) study. This article presents the protocol for a randomised control trial that aims to test the hypotheses that patient-led surveillance results in better health and psychological outcomes than clinician-led surveillance and consumes fewer healthcare resources (if implemented as a replacement rather than an add on to routinely scheduled clinic visits).

### Objectives {7}

#### Primary objective

To assess whether patient-led surveillance (comprising: smartphone supported SSE, teledermatology, fast-tracked unscheduled clinic visits in addition to routinely scheduled clinic visits) compared to clinician-led surveillance (usual care using treating doctor’s usual processes for fast-tracked unscheduled and for routinely scheduled clinic visits) increases the proportion of participants who are diagnosed with a subsequent new primary or recurrent melanoma at a fast-tracked unscheduled clinic visit.

#### Secondary objectives

To assess the impact of patient-led vs clinician-led surveillance on:
Time from randomisation to diagnosis of a subsequent new primary or recurrent melanoma and of a keratinocyte cancer.Psychological outcomes using validated scales for fear of new or recurrent melanoma, general anxiety, stress, and depression.Skin self-examination:I.confidence in, knowledge of, attitudes to, and beliefs about skin self-examination;II.adherence to recommended skin self-examination practice.4.Acceptability of a reduction in routinely scheduled clinic visit frequency.5.Resource use through measurement of:I.number of lesions surgically excised;II.number of follow-up visits attended (both scheduled and unscheduled).

And to:
6.Evaluate the technical performance of two different models of mobile dermatoscope, which patients can attach to their smartphones.7.Assess the acceptability of patient-led surveillance to patients and clinicians (nested qualitative study).8.Assess resource use and costs for healthcare system, patient, and environment (costing study).

### Trial design {8}

This two-arm, parallel, superiority randomised controlled trial will recruit 600 participants with a 1:1 allocation ratio between intervention and control groups (see Fig. 1 for trial flow diagram). A second randomisation step within the intervention arm will randomise participants 1:1 into alternative models of mobile dermatoscopes (polarised or non-polarised light source). This will allow robust evaluation of the technical performance of models with differing price points that represent the range of technologies currently on the market [34]. The primary outcome and secondary outcomes for the intervention group (both models of dermatoscope combined) will be compared to the control group.

**Fig. 1 Fig1:**
[figure not shown]
Study flow diagram

#### Costing study

This will estimate costs to the health care system and to patients for the intervention and control groups. All costs associated with skin self-examination, follow-up clinics, management of newly identified lesions, and any other out of pocket costs will be included. We will provide total costs, and disaggregated costs for different types of activity within the intervention and control groups (e.g. separate cost estimates for fast-tracked unscheduled clinic visits and for routinely scheduled clinic visits). We will also measure and value all resources, and estimate the carbon emissions associated with melanoma surveillance activities in the intervention and control groups using established methods for carbon costing [35, 36]. Further details will be available in the trial’s costing study protocol and health economic analysis plan (manuscript in preparation).

#### Nested qualitative study

A nested qualitative study will explore patients’ and clinicians’ satisfaction with the intervention and its acceptability and explore components which may need to be changed for implementation into routine clinical practice (see section 20a and Supplementary file 3).

## Methods: participants, interventions, and outcomes

### Eligibility criteria {10}

#### Inclusion criteria

Patients who:
Have completed treatment for early-stage (defined as stages: in situ/I/II) melanoma and are attending regular melanoma follow-up as indicated by at least one routinely scheduled visit booked within the next 12 months at a recruiting treatment centre;Are able to conduct SSE;Have a suitable study partner (spouse, partner, family member, friend) to help with SSE;Own a smartphone (and have access to internet, email, and SMS text messaging)Routinely scheduled clinic visit frequency at the treatment centre is 6 monthly or less frequentAre able to give informed consentHas sufficient English language skills to read the materials and complete the questionnairesAre at least 18 years of age

#### Exclusion criteria

Patients who:
Have ever had stage III/IV melanoma.Have a known past or current diagnosis of cognitive impairment.Participated in the MEL-SELF pilot trial (conducted Nov 2018–Feb 2020) [33].Own a smartphone that is not compatible with the mobile dermatoscopes that are part of the intervention.

### Study setting {9}

Individuals who meet the eligibility requirements will be recruited from three sites in New South Wales (NSW), Australia. These are at the Royal Prince Alfred Hospital and the Melanoma Institute Australia (North Sydney), which are specialist-led clinics in metropolitan Sydney, and the Newcastle Skin Check clinic, which is a primary care skin cancer clinic run by general practitioners located in metropolitan Newcastle. Further sites may be opened if needed to meet the recruitment target and may include regional clinics.

### Who will take informed consent? {26a}

Participating clinicians will identify patients attending their clinic who are eligible for the trial. During this consultation, clinicians will discuss the research study with the patient, answer any questions, and identify a target lesion which the participant will monitor during the study (the most concerning or remarkable lesion that the treating doctor would like to monitor for changes). Following this visit, research study staff will email the patient with an invitation package comprising an invitation letter, participant information sheet and a link to an online consent form (eConsent will be provided in an online data collection platform, REDCap [37, 38] hosted by The University of Sydney). Potential participants will be informed that participation is voluntary and that their decision about participating will have no impact on their clinical care. Research study staff will telephone patients who do not complete their consent form within 2 weeks. If the patient does not return their consent form after this telephone call, no further contact will be made, and this information will be recorded.

#### Active run-in phase

Once participants provide eConsent, research study staff will email participants with instructions to:
complete an online baseline questionnaire;log-in to the web-based ASICA skin checker platform, view instructional videos, and undertake guided total skin self-examination and electronic reporting of their findings;upload a macroscopic digital photo using their smartphone of the predetermined target lesion (chosen by the treating clinician) and a photo of their back (to document the amount of sun damage to provide dermatologists with an indicator of melanoma risk) to REDCap.

Eligible patients who consent to participate and complete all the run-in activities within 2 months of consenting, including submission of photos of sufficient quality to allow dermatological assessment, will be randomised.

### Additional consent provisions for collection and use of participant data and biological specimens {26b}

On the eConsent form, participants will be asked for permission for their doctors, other health professionals, hospitals or laboratories, the NSW Cancer Registry, to release information to The University of Sydney concerning their disease and treatment for the purposes of this project. Specific consent for linkage to Medicare claims data will be sought using the Services Australia approved template. Participants will be asked to consent to the storage and use of their skin images during the research project and for future use. Future use may involve further comparison of the performance of the two dermatoscope devices, and comparison of teledermatology reports across different dermatologists. This trial does not involve collecting biological specimens for storage.

### Interventions

#### Explanation for the choice of comparators {6b}

Usual care for early-stage melanoma patients in Australia comprises routinely scheduled visits as recommended by treating clinicians, with the possibility of scheduling additional visits if needed, and information pamphlets on melanoma early detection; therefore, these conditions will be applied to the control arm. The intervention arm will include all the same conditions as the control arm, in addition to teledermatology supported SSE—this is a potential new approach to patient follow-up.

##### Intervention description {11a}

Trial participants in the control arm will receive clinician-led surveillance (usual care), which involves:
An educational booklet ‘Your guide to early melanoma’;Routinely scheduled clinic visits as recommended by their treating clinician (likely to be at intervals between 6 and 12 months);Unscheduled clinic visits, if needed (not prompted through teledermatology)

Trial participants in the intervention arm will receive the intervention (patient-led surveillance) as an adjunct to their usual care, including:
An educational booklet ‘Your guide to early melanoma’;Routinely scheduled visits as recommended by their treating clinician;Unscheduled clinic visits, if needed (not prompted through teledermatology);Continued access to the ASICA skin checker instructional videos on how to perform SSE (including checking for locoregional recurrence) [30, 39];A mobile dermatoscope (with a polarised or non-polarised light source) to attach to their phone, with detailed written and video instructions on how to use the smartphone app and dermatoscopeTraining for themselves and a partner/friend/support person in using the dermatoscope and app, delivered one-on-one by web conferencing;Email or SMS text reminders every 3 months to perform SSE;Teledermatology (see Fig. 2)

**Fig. 2 Fig2:**
[figure not shown]
Teledermatology process

### Criteria for discontinuing or modifying allocated interventions {11b}

The assigned study intervention may need to be modified or discontinued by trial investigators for various reasons including:
Harms and safety issues as detailed in sections 22 and 30.Participant nonadherence. Less frequent submission of images could be offered to participants if necessary.

Study participants will be retained in the trial whenever possible to enable follow-up and measurement of primary and secondary outcomes.

### Strategies to improve adherence to interventions {11c}

Strategies to improve participant adherence to the intervention include:
Participants will receive an overall schedule of trial-related tasks, and automated reminders delivered via text messages (SMS) and emails. These will be supplemented by additional SMS, email, and phone calls from research study staff, if tasks are overdue.There will be detailed initial training and participants will have ongoing access to written and video instructions on the use of the smartphone app and dermatoscope.Participants will have direct access to research study staff via text messaging with phone calls and web-conferencing arranged as needed.

We will report the number and proportion of participants adhering to three-monthly image submission (intervention group only) and using non-trial melanoma surveillance including telehealth and other imaging tests for the skin (intervention and control groups).

### Relevant concomitant care permitted or prohibited during the trial {11d}

There are publicly available apps and other forms of telehealth that assess the risk of melanoma in pigmented lesions using a smartphone camera and automated analysis. Recent systematic reviews have found that these were not of sufficient quality to be recommended, as the apps have low sensitivity in detecting melanoma and may give false reassurance to patients [40, 41]. Current clinical practice guidelines recommend against the use of publicly available melanoma apps. The participant information sheet advises patients that these apps are not recommended. We will measure participant use of non-trial technologies for melanoma detection by questionnaire at 6 and 12 months and will adjust for this at the analysis stage.

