### Statistical methods

#### Statistical methods for primary and secondary outcomes {20a}

A detailed Statistical Analysis Plan will be published separately with a full description of the statistical methods that will be used for analysing the primary and secondary outcomes, planned additional assessments including subgroup and sensitivity analyses, and methods to manage missing data (manuscript in preparation). All analyses will adhere to the intention-to-treat principle, unless otherwise stated. As a secondary analysis, we will also estimate the effect that would have been observed had all participants adhered to the protocol.

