##### Primary outcome

We will use generalised linear models to investigate the difference between patient-led and clinician-led surveillance on the proportion of participants with a subsequent new primary or recurrent melanoma diagnosed through an unscheduled visit. We will present the proportion of participants with the primary outcome in each randomised group, and the between-group difference in proportions, along with the *p* value and 95% confidence interval (CI). Unadjusted and adjusted analyses will also be presented. For the latter, we will include baseline measurements of important risk factors for new or recurrent melanoma as covariates in the model. These will include age, sex, specialist/GP clinic, melanoma substage, subsequent new primary melanoma risk score [48] and dysplastic nevus syndrome. We will check the appropriate assumptions for the model. The adjusted and unadjusted analysis will be presented as an odds ratio along with the 95% CI and *p* value.

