##### Secondary outcomes

We will assess the effect of patient-led and clinician-led surveillance on the secondary outcome of time to diagnosis of a skin cancer (melanoma or keratinocyte cancer), using Cox proportional hazards models. We will present unadjusted and adjusted analyses. For the latter, we will include the same covariates as for the primary outcome (important prognostic variables for outcome event). We will check the proportional hazards assumption using visual inspection of plots (including Schoenfeld residuals) and corresponding test statistics. Other assumptions to be checked include if there is non-informative censoring and if there is a secular trend. All participants will continue to be followed up unless they have withdrawn their consent or moved interstate. In the case that they have withdrawn their consent or moved interstate, participants will be censored at the last available follow-up. The unadjusted and adjusted hazard ratios with 95% CI and *p* values will be reported. If the assumptions including the proportional hazards assumptions are violated, these will be addressed as required. The time to diagnosis will also be analysed allowing for competing risk of death.

The appropriate generalised linear model will be used to assess the remaining secondary outcomes. In general, Poisson regression will be used for count variables, logistic regression for proportions and multiple linear regression for continuous outcome variables. We will assess effects on continuous outcomes (adherence with SSE; thoroughness, confidence, beliefs, attitude and knowledge of SSE; level of fear of new or recurrent melanoma; general anxiety, stress and depression; and acceptability of reducing the frequency of routinely scheduled clinic visits) by including baseline measurement of the outcome as well as other relevant prognostic variables as covariates in the multiple linear regression model. For example, for the outcome: level of fear of new or recurrent melanoma severity, we will include baseline measurement of FCRI severity subscale and personal history of depression or anxiety as covariates. We will estimate the between-group difference in change from baseline for each outcome, together with 95% CI and *p* values. We will check the appropriate model assumptions and if any are violated, then we will use other generalised linear models.

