### Methods in analysis to handle protocol non-adherence and any statistical methods to handle missing data {20c}

Missing data will be accounted for by sensitivity analyses. Each variable will be assessed for missing data and if more than 10% of the data are observed to be missing on key variables, sensitivity analyses will be performed using an appropriate analysis method, such as multiple imputation, instrumental variable analysis or inverse probability weighting [56]. In addition, a per-protocol analysis will be conducted on the primary outcome to estimate the effect that would have been observed had all participants adhered to the protocol.

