## Discussion

This randomised controlled trial will compare patient-led surveillance -with clinician-led surveillance for patients with a history of early-stage melanoma. It will generate evidence on whether patient-led surveillance can safely and effectively enable earlier detection of subsequent new primary or recurrent melanoma and keratinocyte cancers. It will also provide evidence of the acceptability of patient-led surveillance to patients and clinicians and report on the impact on health system resources and patient costs. The study is timely given the growing interest in digital healthcare services during the COVID-19 pandemic.

The investigators have considered the potential risks and impacts of COVID-19 on the conduct of this study. We plan to protect the health of participants and study personnel, while also minimising the impact of our study on the provision of health care, by implementing actions that reduce the requirement for face to face visits either temporarily or permanently. These actions will also protect the scientific integrity of the study.

Clinicians will limit patient face-to-face visits by using routinely scheduled visits to identify potential participants, provide an explanation of the research project to allow informed consent, and select a target lesion. These processes may also be achieved in a telehealth consultation where appropriate. We will minimise participant interactions with researchers. Recruitment packages will be emailed, and consent, questionnaires and diaries will be collected online through REDCap. Images will be uploaded into web-based platforms. Researchers will provide information and support by telephone and offer training on the intervention by video web conferencing. We will supply participants with dermatoscopes via couriers. Study staff will work remotely and meet via video web conferencing when public health advice recommend this. An issue related to the scientific integrity of the trial is that there may be more background telehealth use and alternative app use than previously. We plan to collect this information from participants in the baseline and follow-up questionnaires.

In conclusion, this study will contribute novel findings on evidence-based follow-up after treatment of early melanoma, to maximise patient wellbeing and the early detection of new or recurrent melanoma, while minimising costs to the patient and health system.

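### The protocol promises to adjust for outside melanoma technology use reported at 6 and 12 months, without naming the analysis; applied to the randomised comparison, this can bias the estimated effect of assignment

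*Protocol article*

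**What the plan says.** Four parts of the protocol article bear on this point.

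- **Concomitant care {11d}.** Participants will be asked about their use of "non-trial technologies for melanoma detection by questionnaire at 6 and 12 months and will adjust for this at the analysis stage". The commitment is firm. It is not tied to a sensitivity, per-protocol or mediation analysis, and no method is named.
- **Statistical methods {20a}.** The default is set by "All analyses will adhere to the intention-to-treat principle, unless otherwise stated". For the adjusted primary model, "we will include baseline measurements of important risk factors for new or recurrent melanoma as covariates in the model". The list begins "These will include age, sex, specialist/GP clinic, melanoma substage, subsequent new primary melanoma risk score" and ends with dysplastic nevus syndrome. For time to diagnosis, "we will include the same covariates as for the primary outcome". Outside technology use is not on the list. For the primary outcome, "Unadjusted and adjusted analyses will also be presented".
- **Protocol non-adherence and missing data {20c}.** Separately, "a per-protocol analysis will be conducted on the primary outcome". Section {11d} does not link its adjustment to that analysis.
- **Discussion.** On background telehealth and alternative app use, the article says "We plan to collect this information from participants in the baseline and follow-up questionnaires". A measure taken before randomisation is therefore planned, although {11d} does not mention it.

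Section {11c} already commits to reporting the number and proportion of participants in both arms who use melanoma surveillance from outside the trial.

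**The concern.** A covariate is safe in a randomised comparison when allocation cannot affect it. Outside technology use reported at 6 and 12 months does not meet that condition, for three reasons.

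1. Participants know their allocation. Only the intervention arm receives a dermatoscope and teledermatology, so either arm may turn to outside apps or telehealth more or less often because of what it was given.
2. Noticing a suspicious lesion can prompt both outside use and an unscheduled clinic visit. A melanoma diagnosed at such a visit is the primary outcome.
3. The outcome accrues over the same 12 months, so use reported at either questionnaire may come after the diagnosis or result from it.

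A model that conditions on this variable need not estimate the effect of being assigned to patient-led surveillance. Outside help sought by control participants is also part of what usual care means here, so adjusting it away changes the question. The analyst is left with two descriptions of adjustment that do not match and no statement of which one governs.

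**Working it through.** **Step 1: the plan's own figure.** The documents give no number for this adjustment. The nearest figure is the sample size, which shows whether the fix would disturb the design. Inputs from {14}: 1% versus 6%, two-sided 5% level, Fisher's exact test, 1:1 allocation. Exact enumeration gives 79.9% power at 225 per arm and 80.1% at 226, so 226 per arm (452) reproduces. Inflation gives 452 / 0.75 = 603, against 600 stated. The calculation is for an unadjusted comparison and does not depend on any covariate.

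**Step 2: the passages side by side.** Section {11d} promises adjustment for a variable measured at 6 and 12 months. Section {20a} lists six baseline covariates for the primary outcome and reuses them for time to diagnosis. Neither section refers to the other, and nothing withdraws or restricts the promise in {11d}.

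**Step 3: illustration with no true effect.** Every input is an assumption, because the documents give no usage rates.

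- 10% of participants in each arm have a worrying lesion.
- Outcome risk is 30% with such a lesion and 0.5% without, so the risk in each arm is 0.10 × 0.30 + 0.90 × 0.005 = 3.45%. The true odds ratio is 1.
- Outside use among participants with a worrying lesion: 60% in control, 20% in intervention.
- Outside use among everyone else: 10% in both arms.
- Use itself has no effect on the outcome.

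Expected cells as a fraction of each arm:

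| Stratum | Control: outcome / total | Intervention: outcome / total |
|---|---|---|
| Users | 0.01845 / 0.15 (12.3%) | 0.00645 / 0.11 (5.86%) |
| Non-users | 0.01605 / 0.85 (1.89%) | 0.02805 / 0.89 (3.15%) |

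For example, control users are 0.10 × 0.60 + 0.90 × 0.10 = 0.15, with outcomes 0.06 × 0.30 + 0.09 × 0.005 = 0.01845.

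The Mantel-Haenszel odds ratio is Σ(ad/N) / Σ(bc/N), where a and b are intervention participants with and without the outcome, c and d are the same for control, and N is the stratum total. The users contribute 0.00326 and 0.00735, the non-users 0.01344 and 0.00795. The result is 0.01671 / 0.01530 = **1.09**. A logistic model with allocation and use also gives 1.09.

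Varying only the use rates among participants with a worrying lesion:

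| Control / intervention use | Pooled adjusted OR (truth 1.00) |
|---|---|
| 40% / 20% | 1.03 |
| 40% / 10% | 1.04 |
| 60% / 20% | 1.09 |
| 60% / 10% | 1.10 |
| 40% / 40% or 60% / 60% | 1.00 |
| 20% / 60% (reversed) | 0.92 |

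The direction follows the imbalance in use between the arms.

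**Step 4: a second set of assumptions.** A latent vigilance trait is present in 30%, with an odds ratio of 4 for use and 4 for the outcome. Overall use is 30% in one arm and 10% in the other, in either direction.

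- No true effect (3% in both arms): adjusted OR 0.91 or 1.10 if use does not affect the outcome. It is 0.75 or 1.34 if use itself doubles the odds of the outcome, which is a further assumption.
- Design effect (1% versus 6%): the true OR is (0.06/0.94) / (0.01/0.99) = 6.32 and the true difference is 5.0 points. The adjusted OR runs from 4.79 to 8.57, and the standardised difference from 4.1 to 6.0 points.
- Equal use (20% in both arms), with no effect of use on the outcome: adjusted OR 6.33 and difference 5.0 points, so essentially no bias.

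**The case against.** The strongest reply is that {11d} does not say which analysis it means. The primary model's covariates are listed elsewhere without this variable, a separate per-protocol analysis is planned in which discouraged outside technology might belong, and full methods are deferred to a statistical analysis plan. The unadjusted estimate is reported in any case. The illustrated bias is also small against sampling error: at 3.45% risk and 300 per arm, the standard error of the log odds ratio is √[2 × (1/10.35 + 1/289.65)] = 0.45, so a shift to 1.09 (log 0.086) is about 0.2 standard errors.

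Much of this stands, and it limits what can be claimed. Four stronger readings are tempting, and the documents do not support them.

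- **That a baseline-only rule is broken.** Section {20a} says which baseline covariates will be included; it never says that only these may be. The sections are unreconciled, which is less than a breach.
- **That intention to treat is abandoned.** The principle allows stated exceptions, and the unadjusted randomised comparison is kept.
- **That the adjusted result is certain to be biased.** Bias needs use to differ by arm or to be affected by the outcome. Both are plausible, and neither is documented.
- **That up to 150 of the 600 would drop out of the adjusted model.** The 25% allowance in {14} covers withdrawal and dropout and is already built into the 600. It is not a questionnaire non-response rate, and {20c} offers multiple imputation as one option when more than 10% of a key variable is missing.

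The reply does not remove the promise itself. An unrestricted statement that the trial will adjust is an analysis decision that a later plan could inherit, and no text ties it to the per-protocol analysis.

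**Conclusion.** The point holds in a limited form. Section {11d} fixes an adjustment for a post-randomisation variable and leaves the analysis and estimand open. If it is applied to the randomised comparison, it can bias the estimated effect of assignment. Neither direction nor size can be derived from the documents.

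Under the Step 3 assumptions the distortion of a null effect is modest, about 1.03 to 1.10 with more use in control. It becomes larger if use itself affects the outcome, and vanishes when use is balanced between arms and unaffected by the outcome. The retained unadjusted analysis limits the damage, but it does not settle which adjusted model is to be reported beside it.

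**What to change.** 1. In {11d}, remove the commitment to adjust as far as it concerns the intention-to-treat comparisons. Keep the baseline covariates listed in {20a} for the primary outcome and for time to diagnosis.
2. If adjustment for outside technology is wanted there, add only the baseline questionnaire measure mentioned in the Discussion, and name it in the covariate list in advance.
3. Report use at 6 and 12 months descriptively by arm, as {11c} already plans.
4. Confine any adjustment for follow-up use to a supplementary analysis that is labelled as such, states its own estimand, and uses a method suited to post-randomisation variables.

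The cost is a sentence or two in the protocol, carried into the statistical analysis plan. No new data are needed, and the 226 per arm and 600 in total stay as they are.
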